## Abstract

**Background:**

Despite the growing popularity of massage, its effectiveness for treating neck pain remains unclear, largely because of the poor quality of research. A major deficiency of previous studies has been their use of low “doses” of massage that massage therapists consider inadequate. Unfortunately, the number of minutes per massage session, sessions per week, or weeks of treatment necessary for massage to have beneficial or optimal effects are not known. This study is designed to address these gaps in our knowledge by determining, for persons with chronic neck pain: 1) the optimal combination of number of treatments per week and length of individual treatment session, and 2) the optimal number of weeks of treatment.

**Methods/design:**

In this study, 228 persons with chronic non-specific neck pain will be recruited from primary health care clinics in a large health care system in the Seattle area. Participants will be randomized to a wait list control group or 4 weeks of treatment with one of 5 different dosing combinations (2 or 3 30-min treatments per week or 1, 2, or 3 60-min treatments per week). At the end of this 4-week primary treatment period, participants initially receiving each of the 5 dosing combinations will be randomized to a secondary treatment period of either no additional treatment or 6 weekly 60-min massages. The primary outcomes, neck-related dysfunction and pain, will be assessed by blinded telephone interviewers 5, 12, and 26 weeks post-randomization. To better characterize the trajectory of treatment effects, these interview data will be supplemented with outcomes data collected by internet questionnaire at 10, 16, 20 and 39 weeks. Comparisons of outcomes for the 6 groups during the primary treatment period will identify the optimal weekly dose, while comparisons of outcomes during the secondary treatment period will determine if 10 weeks of treatment is superior to 4 weeks.

**Discussion:**

A broad dosing schedule was included in this trial. If adherence to any of these doses is poor, those doses will be discontinued.

**Trial registration:**

This trial is registered in ClinicalTrials.gov, with the ID number of NCT01122836

## Background

Neck pain is a common health problem in the United States and other developed countries. An estimated 70% of adults are afflicted by neck pain at some time in their lives
[1,2], 30 to 50% of adults are bothered by neck pain each year,
[3] 10 to 15% of adults report neck pain that has persisted more than 6 months in the past year,
[1,4] and 5% of adults are currently experiencing disabling neck pain
[2]. A recent survey found that 25% of Canadians who had back and/or neck pain had sought care for their condition in the prior month, and that those with more severe pain were substantially more likely to seek care
[5]. Another study found care seekers with chronic neck pain were most likely to visit primary care providers (72%) chiropractors (40%), physical therapists (35%), orthopedic surgeons (32%) and massage therapists (28%)
[6]. Neck pain is the second leading health-related reason for time off work, after low back pain,
[7] and millions of dollars are spent annually on treatment, lost wages, and compensation for neck pain
[8,9].

As with back pain, a plethora of options are available for treating neck pain, yet the most commonly used treatments lack consistent evidence of effectiveness, especially for persons with chronic neck pain
[6]. Standard medical practice employs rest, medication, physical medicine modalities, and education
[10,11]. Medications, especially non-steroidal anti-inflammatories, and referral for physiotherapy were the most common treatments used by general practitioners in a recent study of how primary care physicians diagnose and treat patients with chronic neck pain
[12]. Treatment effects, even for therapies demonstrating “benefit”, are typically small and it remains unclear if treatment benefits persist beyond 6 months
[13].

With the paucity of proven conventional treatments, it is not surprising that neck pain is one of the top two conditions (second to back pain) for which American adults use CAM therapies,
[14-16] most commonly chiropractic or massage. Almost 1 in 4 chiropractic visits and 1 in 5 massage visits are for neck symptoms
[16,17] and only back pain is more commonly treated by these professions
[17]. However, the effectiveness of massage for neck pain has not clearly been established. A recent systematic review evaluating the benefits of massage for mechanical neck disorders concluded that “the contribution of massage to manage cervical pain remains unclear”
[18]. Only 6 of the 19 studies included in this review focused on massage as the sole treatment and only 4 of these 6 studies offered more than one treatment session. These 4 studies each examined a different type of massage and used a different treatment schedule. In fact, none of the 19 studies evaluated a type of massage that Americans would normally receive for neck pain. Given the generally low “dose” of massage, the heterogeneous treatment protocols, the frequent inclusion of other treatments, and the failure to study massage treatments for neck pain as they are currently provided in the U.S., it is not surprising that, despite 19 small trials, the benefits of massage remain unclear. The review recommended that researchers establish optimal dosing parameters for massage and test them in preliminary studies before undertaking large clinical trials
[18]. A more recent review of 10 trials comparing massage to a control or other treatments for sub-acute and chronic neck pain concluded that massage was effective for relieving neck pain and related symptoms immediately post-treatment, but data on longer term outcomes were not available
[19].

This study, designed to provide a firm foundation for more rigorous research on massage in the future and using a massage protocol that includes techniques that are used by massage therapists in the US, will determine the optimal minimal dose of therapeutic massage for chronic neck pain. We will evaluate three key components of optimal dosing: length of each treatment session, frequency of treatments per week, and the total treatment period. The specific aims are:

1. To determine the optimal combination of frequency of treatment and length of treatment

2. To determine the optimal duration of the treatment period

## Methods/design

### Overview

This trial was designed to determine the optimal dose of massage for persons with chronic non-specific neck pain. We conceptualize “dose” as including a specific weekly frequency of treatment, length of each treatment session and number of weeks of treatment. We conceptualize the “optimal dose” to be the minimal dose offering the most benefit but still having adequate adherence to treatment (i.e. at least 80% of participants in a dose attending at least 75% of the treatment sessions without serious adverse events possibly attributable to massage). In the trial, 228 study participants will be recruited and randomized to either a wait list control group or to 4 weeks of treatment with one of 5 different weekly dosing combinations (with 38 persons per group). At the end of 4 weeks (the primary treatment period), participants in each of the 5 different dosing combination groups will be randomized to receive either no additional treatment or to weekly 60-min massages for an additional 6 weeks (the secondary treatment period). Participants in the waitlist group will receive four weekly 60-min massages.

Telephone interviewers unaware of treatment assignment will assess functional status and pain at 5 weeks post-randomization (end of primary treatment period) and again after 12 weeks (end of secondary treatment period) and 26 weeks. To more completely characterize the course of treatment effects, we will also collect data on the primary outcomes using internet questionnaires at 10, 16, 20 and 39 weeks. Figure
1 depicts the basic study design.

**Figure 1 F1:**
[figure not shown]
Participant focused flow chart.

### Rationale for dosing schedule

We chose a primary treatment period of 4 weeks because our small randomized trial found
[20] clinically important improvement among massage recipients by 4 weeks when receiving one 60 min massage per week. By having 5 groups receiving different doses over the first 4 weeks, we will be able to determine which weekly dose is optimal during this period. A secondary treatment period of 6 weeks was chosen because in our previous trial, up to 10 treatments were given over a period of 10 weeks. This will allow us to evaluate the benefits of an additional 6 weeks of treatment (with weekly 60-min doses).

This study design allows an examination of 5 doses that cover a broad range of feasible frequency/week (1, 2, 3 times) and treatment lengths (30 and 60 min). In order to test doses within the full range of likely beneficial doses, the dose range begins with the dose found effective in our pilot trial
[20] (i.e., 60 min/week) and includes higher doses than those experienced massage therapists typically employ in their practices. We did not include 90 min visits because massage therapists were concerned that such a long treatment might aggravate the neck. By including doses that substantially exceed common practice, we can be more confident that we have probably included the “optimal dose”.

### Study population

Participants will be recruited from potentially eligible persons in the metropolitan Seattle area who receive care at Group Health, an integrated health care system that serves over 400,000 members through its own primary care facilities in Western Washington, and from the general population of the Seattle metropolitan area. Eligible individuals will have non-radicular uncomplicated chronic neck pain of non-specific origin. Neck pain due to infectious, inflammatory, spinal stenosis, and neoplastic causes, which are rare, will be explicitly excluded in this group of adults between 20 and 64 years of age.

### Inclusion and exclusion criteria

Inclusion and exclusion criteria were developed with the goal of maximizing enrollment of appropriate participants while screening out patients: who have neck pain of a specific (e.g. spinal stenosis) or complicated (e.g. due to a medical condition) nature, for whom massage is contraindicated (e.g. previous stroke), or whose medical conditions might make it difficult or impossible to receive the treatments (e.g. gross obesity or severe psychiatric conditions). These criteria (Table
1) are intended to exclude patients with medical conditions that: might contribute to an increased risk of a severe adverse event, would not allow for fully informed consent, or might lead to misinterpretation of the data (e.g. neuropathy of the hands because it might interfere with pain sensation).

**Table 1 T1:** Inclusion and exclusion criteria

**Inclusion criteria**	**Exclusion criteria**
Between 20 and 64 years of age (Older people have higher risk of undiagnosed serious conditions causing neck pain)	Previous massage for neck pain in the last year or any massage in the last 3 months
Both men and women, any race or ethnicity	Neck pain lasting less than 3 months
At least one primary care visit for neck pain within the past 3 – 12 months	Mild symptoms and no functional impairment (less than 4 on a 0 to 10 pain intensity scale and less than 5 on the Neck Disability Index)
Non-specific, uncomplicated neck pain, i.e., ICD-9	Identifiable disease or condition could be the cause of neck pain (metastatic cancer or unexplained weight loss, discitis, disk herniation, vertebral fracture, infectious cause of neck pain, severe or progressive scoliosis, spondylolishthesis, spinal stenosis, osteoporosis)
codes: 723.1 Cervicalgia	
847.0 Cervical strain or sprain	
839.00-839.08 Cervical subluxation	Complicated neck problem (cervical radiculopathy, previous neck surgery, motor vehicle accident within past 3 months) Medico-legal issues (seeking or receiving compensation/litigation for neck or back pain)
722.4 Cervical intervertebral disc degeneration	
721.0 Cervical spondylosis without myelopathy	Other conditions that might confound treatment effects or interpretation of the results (e.g., disabling heart or lung disease, diabetic neuropathy, severe fibromyalgia, severe untreated depression, receiving treatment for hepatitis or AIDS, rheumatoid arthritis, planning to seek CAM or medical treatments for neck pain)
Symptoms consistent with non-specific, uncomplicated neck pain	
Lives or works within 45 minutes travel time from study clinic	Potential contraindications for massage (pregnancy, dizziness while lying supine, symptoms consistent with transient ischemic attack (TIA), previous stroke, hypersensitivity to touch or loss of sensation)
Give informed consent	Conditions making informed consent or treatment difficult (dementia, unable to read or speak English, paralysis, physically unable to undergo massage sessions – e.g., cannot get on/off massage table, major psychoses, severe problems with hearing or vision, lack of transportation, scheduling problems, plan to move out of town)

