### Randomization to treatment group

A total of 228 participants with neck pain will be randomized (38 to each of the 6 study groups). After collecting baseline data, the Research Specialist will electronically randomize participants to treatment group. Treatment groups will be assigned by a computer-generated sequence of random numbers using a program that ensures that treatment allocation cannot be changed after randomization. Participants will be randomized in blocks of varying size to ensure balanced but unpredictable assignment of participants to all treatment groups. The computer will be programmed to randomize within two strata based on the baseline value of neck dysfunction as measured by the Neck Disability Index (5 to 14 and 15+).

After 4 weeks of treatment, individuals within each of the 5 treatment groups (Groups 2–6) who complete the 5 week outcome assessment will again be randomized, within group, to receive 6 more weekly 60 min sessions or no additional treatment. This will be done using independent block randomization, with stratification by baseline value of neck dysfunction, so that there are approximately equal numbers of participants in each treatment group randomized to additional treatment and to no additional treatment. This second randomization will allow us to evaluate the benefits, if any, of 6 weeks of additional treatment. Because Group 1 (wait list controls) had been promised massage treatment after the waiting period, they will receive weekly 60 min massages for 4 weeks.

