#### Primary outcomes

Primary outcomes will be measured at 5, 12 and 26 weeks by telephone and at 10, 16, 20 and 39 weeks by internet survey. We will use the Neck Disability Index (NDI),
[23] a 10-item questionnaire that was adapted from the popular Oswestry Index for back pain, to assess neck pain and dysfunction. The NDI measured at 5 weeks will serve as our primary time outcome. The NDI’s psychometric properties are better characterized than those of other neck specific questionnaires, even though it has the possible disadvantage of combining assessments of pain and dysfunction, which are separate dimensions. Because the NDI requires reading six moderately long response options for each question, we will send participants copies of the NDI before we administer the baseline and follow-up interviews and also post a copy on a section of the Group Health Research Institute website that is accessible by study participants.

We will measure pain intensity using a 0 to 10 scale, where 0 represents “no pain” and 10 represents “pain as bad as it can be”. Participants will be asked at baseline and during all follow-up interviews to rate the average intensity of their neck pain during the previous week. Such scales are positively correlated with other measures of pain intensity and have demonstrated sensitivity to change
[24].

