### Statistical issues

#### Sample size and the detectable difference

Our sample was chosen to ensure adequate power to detect a significant difference between at least two of the 5 groups receiving a massage treatment in the first 4 weeks of the trial (and not just adequate power to find a difference between one or more of the treatment groups and the waitlist control group). This reflects the primary goal of the trial: to compare the effects of different doses of massage on neck-related disability, and not just to determine if massage is better than no-additional treatment (as in the waitlist control). Our primary outcome is the binary measure of clinically relevant improvement of at least 5 points on the Neck Disability Index (NDI) at 5 weeks compared to baseline NDI score
[31]. Based on findings in our pilot study, we assumed that 7% of the waitlist control group and 35% of Group 2 (60-min weekly treatment) would improve. We lack pilot data to estimate improvement rates in the other groups. Therefore, to permit sample size estimation, we will assume that treatment benefits will increase with the number of treatments given per week (for a fixed weekly dose) and with the number of minutes of massage per week. We assume a two–fold improvement from the lowest to the highest weekly dose (i.e., 60 to 180 min), based on the expectations of our consultant massage therapists. Table
4 summarizes our assumptions for both the NDI and neck bothersomeness score.

**Table 4 T4:** Assumptions for sample size calculations

**Group**	**Amount of massage (weekly dose)**	**Proportion with clinically relevant improvement on NDI (at least 5 point improvement)**	**Proportion with clinically relevant improvement on Bothersomeness score (≥ 30% improvement)**
1	Waitlist	0.07	0.10
2	60 min 1×/week (60 min)	0.35	0.48
3	30 min 2×/week (60 min)	0.40	0.55
4	60 min 2×/week (120 min)	0.55	0.65
5	30 min 3×/week (90 min)	0.60	0.70
6	60 min 3×/week (180 min)	0.70	0.80

To protect against multiple comparisons, we will use Fisher’s protected least significant difference approach. Although this approach has been shown to inadequately protect against the type I error rate for studies with more than 3 groups,

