[32] we ran several simulations to test the type I error rate for our specific study design of 6 groups, with a binary outcome. We did this for sample sizes ranging from 30 to 40 and assuming an overall baseline improvement rate of either 0.07 or 0.50. We found that the type I error remained below 0.05 for all these situations. Following Fisher’s protected least significant approach, we will first use the omnibus Chi-Square test to test if there is any significant difference between all 6 groups and, if we find one, we will test for pairwise differences between groups. With 34 participants per group, we will have 97% power to find a significant difference between at least two of the 6 groups and 80% power to find a significant difference between Group 6 and Group 2, the treatment groups assumed to differ most in proportion of improvement. Assuming 10% loss to follow-up (as found in our pilot study and in our studies of back pain), we plan to recruit 38 participants in each group, for a total sample size of 228 in the trial.

Our other primary outcome is improvement in the Neck Pain Intensity Score of at least 30% from baseline, which reflects clinically important improvement
[33]. With a final sample size of 34 participants in each group we would have 99% power to find a significant difference between at least two of the 6 groups and 80% power to find a significant difference between Group 6 and Group 2 assuming improvement rates as outlined in Table
4. Therefore, we will have adequate power to assess both our primary outcomes.

It should be noted that both primary outcomes (function and symptoms) will be tested at each time point at the 0.05 level because they address separate scientific questions. Analyses of both outcomes at all follow-up times will be reported, imposing a more stringent requirement than simply reporting a sole significant
[34].

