##### Primary treatment period: primary study outcomes at 5 weeks

The primary analyses will look at binary outcomes: 1) improvement of at least 5 points from baseline Neck Disability Index score and 2) improvement of at least 30% from baseline on the pain intensity score. We will use the following logistic regression model,

(1.1)$$\;\begin{array}{cc} \text{logit}\left(Y_{i}\right) & =\beta_{0}+\beta_{1}Group2_{i}+\beta_{2}Group3_{i}\\ & \;+\beta_{3}Group4_{i}+\beta_{4}Group5_{i}\\ & \;+\beta_{5}Group6_{i}+\alpha {Ζ}_{i} \end{array}$$

where *GroupA*_*i*_ is an indicator variable of 1 if participant i was randomized to group A or 0 otherwise (A=2, 3, 4, 5, or 6) and Z_*i*_ is a vector of potential confounders including baseline outcome score. We will use the Fisher’s protected least significant approach to assess if there are any differences among the 6 Groups and then, if there is a significant difference, to assess if any pairwise differences are significant. It is also of interest to run a parametric model to evaluate a trend over the weekly dose while taking into account the number of visits. In standard dosing analyses, at the lower doses, the proportion of patients improves with increasing dose, but as the dose increases to some higher level, further improvement is attenuated and approaches a threshold (see Figure
2).

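### The joint mild-symptom exclusion lets in people with pain of 4 or more and NDI 0–4, who have no randomisation stratum and cannot reach the 5-point NDI outcome

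*Protocol article*

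**What the plan says.** Table 1 (Inclusion and exclusion criteria) lists as an exclusion "Mild symptoms and no functional impairment", and spells it out as "less than 4 on a 0 to 10 pain intensity scale and less than 5 on the Neck Disability Index". Both the label and the definition are joint conditions.

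The section Randomization to treatment group has the computer "randomize within two strata based on the baseline value of neck dysfunction as measured by the Neck Disability Index (5 to 14 and 15" or more). The second randomisation, after the 5-week assessment, is also stratified by baseline neck dysfunction.

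Sample size and the detectable difference states: "Our primary outcome is the binary measure of clinically relevant improvement of at least 5 points on the Neck Disability Index (NDI) at 5 weeks". The section on the 5-week analysis repeats it as "improvement of at least 5 points from baseline Neck Disability Index score". The second primary outcome is a pain improvement of at least 30% from baseline.

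The Statistical analysis section makes intention to treat, with all participants, the primary analysis. The inclusion column of Table 1, the telephone screen and the nurse's examination (Recruitment procedures and eligibility assessment) give no minimum NDI.

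**The concern.** The strata presuppose that everyone randomised has an NDI of at least 5. The entry criteria do not ensure this, because an NDI below 5 excludes a person only when pain is also below 4. One group falls between the two rules: pain of 4 or more with NDI 0–4.

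One of two things then happens to such a person. They may pass screening and reach a randomisation program that has no stratum for them. Or they may be allocated somehow, in which case they count in the denominator of the NDI responder rate in whichever arm they join but can never count in the numerator. The first is an operational failure after consent and baseline interview. The second lowers the responder rates and costs power for the dose comparisons. Telephone screening follows a computer program, and one built on Table 1 as worded would let these people through. The natural history cohort uses the same criteria, so it inherits the gap in entry.

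**Working it through.** **Step 1: who is eligible.** Inputs are the Table 1 limits, a pain scale of 0–10, and an NDI of ten items with six response options each (Primary outcomes). The lower end of 0 and upper end of 50 for the NDI are assumed from standard scoring.

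- Rule as written: excluded if pain < 4 and NDI < 5.
- Pairs with NDI < 5 that stay eligible: pain 4–10 (7 values) × NDI 0–4 (5 values) = 35 score pairs.
- NDI 0–4 with pain 0–3 is excluded, so the gap exists only at pain of 4 or more.
- With a separate requirement of NDI ≥ 5, the number of such pairs is 0.

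**Step 2: strata and outcome for those pairs.** The strata are 5–14 and 15 or more, so none of the 35 pairs has one. The largest possible NDI improvement from a baseline of 4 is 4 − 0 = 4 points, and 4 < 5, so none can be an NDI responder.

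**Step 3: reproduce the plan's figures.** Inputs are the NDI response rates 0.35 (Group 2) and 0.70 (Group 6) from Table 4, 34 per group, and a level of 0.05, taken as two-sided.

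- Sample size: 34 / 0.90 = 37.8, so 38 per group, and 6 × 38 = 228. This matches.
- Power: for each pair of responder counts a and b, the Wald statistic for the log odds ratio is |ln(a/(34−a)) − ln(b/(34−b))| / √(1/a + 1/(34−a) + 1/b + 1/(34−b)). Summing the binomial probabilities of all pairs where this exceeds 1.96 gives 81.9%, within 2 points of the stated 80%.
- Cross-check by the pooled normal formula: the mean rate is 0.525. The null standard error is √(2 × 0.525 × 0.475 / 34) = 0.1211 and the alternative one is √((0.35 × 0.65 + 0.70 × 0.30) / 34) = 0.1134. Then (0.35 − 1.96 × 0.1211) / 0.1134 = 0.99, which gives 84.0%. The exact Pearson chi-square gives 82.8% and Fisher's exact test 76.4%.

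**Step 4: illustrative dilution.** Let a share f of each arm have NDI 0–4. The article gives no value for f, so this range is assumed. Each response rate becomes rate × (1 − f).

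| f | Group 2 | Group 6 | Power, exact Wald | Power, pooled normal |
|---|---|---|---|---|
| 0 | 0.350 | 0.700 | 81.9% | 84.0% |
| 2% | 0.343 | 0.686 | 80.0% | 82.3% |
| 5% | 0.3325 | 0.665 | 77.2% | 79.6% |
| 10% | 0.315 | 0.630 | 72.6% | 75.0% |

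In people, 2%, 5% and 10% of 228 are about 5, 11 and 23.

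**The case against.** The strongest reply is that the strata themselves show that an NDI of at least 5 was meant for everyone, so this is a slip of wording. A person with NDI 0–4 would then most likely be caught as a screen failure or a query at randomisation, would never enter the analysis and would dilute nothing. That stands as far as it goes: failure to be placed and dilution are alternatives and cannot both happen to the same person. It does not remove the contradiction, because the entry rule and the strata are both stated and do not agree.

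The size is also open to challenge, and rightly. The article notes that the NDI mixes pain with dysfunction, so pain of 4 or more together with an NDI below 5 may be uncommon. The Group 2 rate comes from a pilot whose entry criteria are not shown; if similar people were in it, the 35% already reflects them and the discount in step 4 counts them twice. The planned model adjusts for the baseline score, which could recover some of the loss. People with NDI 0–4 can still respond on pain.

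A reader might go further and infer that the joint wording is wrong on the pain side too, so that either limit alone should exclude. The same wording does admit people with NDI of 5 or more and pain of 0–3. From a baseline of 1, 2 or 3, a one-point fall is 100%, 50% or 33% and meets the 30% threshold, whereas from 4 it is 25% and does not. The documents do not make this an error. These people have a stratum and can reach the NDI outcome, and the label of the exclusion appears to keep those who are functionally impaired but have milder pain. Only a baseline pain score of 0, where a percentage change is undefined, leaves something to settle.

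**Conclusion.** The point holds as an internal contradiction between Table 1 and the randomisation strata, with a consequence for the primary NDI outcome. It is confined to people with pain of 4 or more and NDI 0–4. It rests on the literal reading of a criterion whose label and definition agree with each other, and, for the outcome, on an NDI floor of 0.

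The effect on power is unknown. If no such person is randomised there is none. At a 2% share the exact Wald figure equals the protocol's 80%, and at 5–10% it would be about 77% to 73%. These are illustrations and not estimates. A reader might infer that the trial is shown to be underpowered or that every dose contrast is biased. The documents support neither: the share is not given, and any such participants would be spread by randomisation across all arms.

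**What to change.** Reconcile Table 1 with Randomization to treatment group by making a baseline NDI of at least 5 a stand-alone entry requirement. Check it on the same baseline NDI that assigns the stratum. The article confirms eligibility before the baseline questionnaire is given, so a score that passes at screening could still fall below 5 at baseline. Carry the same wording into the screening program and the natural history cohort.

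For pain, no minimum is needed to resolve the contradiction. One sentence on how the 30% outcome is scored when baseline pain is 0 would be enough.

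The cost is a line in the criteria, an edit to the screening program, and the loss of otherwise eligible people with pain of 4 or more and NDI 0–4. Their number is not given but is probably small. It is best settled before enrolment, because later repair would mean excluding people after randomisation.
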